## **2.6.2 Post-randomisation withdrawals, exclusions and moves out of region**

### **Withdrawal:**

Participants may be discontinued from the trial treatment and/or the trial at any time without prejudice. Unless a participant explicitly withdraws their consent, they should be followed-up wherever possible and data collected as per the protocol until the end of the trial. For participants explicitly withdrawing consent for follow up procedures, trial data obtained up until the point of withdrawal will be included in the final analysis of the study. Participants will have the option to withdraw from the trial-related questionnaires, but continue to provide routine NHS data for the purposes of the trial e.g. hospital records of subsequent treatment for the ankle fracture.

Participants who withdraw will not be replaced in the trial and a corresponding withdrawal CRF will be completed by the Trial Manager.

Participants may be withdrawn from the trial at the discretion of the investigator and/or Trial Steering Committee due to safety concerns.

### **Follow up:**

Outcome questionnaires can be completed over the telephone, if postal copies are not returned. Text messages will be sent to participants to inform them that a questionnaire is due or on its way. Text messages will only be sent to those participants who have given their prior consent to this by initialling the corresponding box on the consent form and providing their mobile telephone number. Details pertaining to the timing and nature of planned follow up procedure for telephone/post/text message are further detailed in the data management plan.

## **2.7 Trial treatments / intervention**

### **2.7.1 Trial treatment(s) / intervention**

All participants who require ankle fixation will have this performed according to the preferred technique of the operating surgeon. The details of the surgery will be left to the discretion of the surgeon to ensure that the results of the trial can be generalised. However, a suitably trained member of the research team will complete details of the procedure undertaken within the baseline CRF. All participants will then receive normal local care until satisfactory clinical wound check (usually two weeks post operatively, up to maximum three weeks), at which point the intervention will be applied by a suitably trained member of the trauma team.

All participants not receiving surgery will be approached to take part in the trial on first presentation to the trauma team fracture clinic, and will be eligible for trial participation up to a maximum of 3 weeks from injury.

Weight bearing status will be at the discretion of the treating member of the trauma team and recorded on subsequent CRFs.

### **Control Group - Standard Plaster Cast:**

All participants in the control arm will be fitted with cast immobilisation for a minimum of three weeks. It is expected that the control intervention will not exceed eight weeks, however this will be recorded and monitored by the TMG.

### **Intervention Group – Functional Bracing:**

All participants in the intervention arm will be fitted with a FARO for a minimum of three weeks. It is expected that the intervention will not exceed eight weeks, however this will be recorded and monitored by the TMG. Throughout this period participants will be encouraged to remove their functional brace to complete active unloaded ankle range of movement exercises. An information sheet explaining these exercises will be handed out to all participants randomised to this trial arm.

Rehabilitation:

Following the trial intervention period, in this pragmatic trial, any other rehabilitation input (including a formal referral to physiotherapy) will be left to the discretion of the treating trauma team member. However, a record of any additional rehabilitation, together with a record of any other interventions will be recorded on follow up CRFs.

### **2.7.2 Compliance**

Quality assurance checks will be carried out via CRF completion to assess compliance with the above intervention delivery. Any deviations noted from the outlined trial interventions will be monitored by the TMG. If required further training will be implemented to resolve any inconsistencies.

## **2.8 Blinding**

### **2.8.1 Methods for ensuring blinding**

As the type of rehabilitation used is clearly visible, the participants cannot be blind to their treatment. In addition, the treating clinical team cannot be blind to the treatment, but will take no part in the assessment of potential participants.

The questionnaire data will be collected and entered onto the trial central database via phone and postal mechanisms by a suitably trained member of the research team for all data points. The inputting member of the research team cannot be blinded to the trial interventions, however data will be presented to the DMC using a combination of open and closed reports that will be further detailed in the SAP.

## **2.9 Concomitant illness and medication**

### **2.9.1 Concomitant illness**

Details of any concomitant illness will be recorded at trial entry.

### **2.9.2 Concomitant medication**

Details of concomitant medication will be recorded at trial entry, as detailed in the baseline CRF.

## **2.10 End of trial**

The trial will end when all participants have completed their 24 month follow-up.

The trial will be stopped prematurely if:

- Mandated by the Ethics Committee
- Following recommendations from the Data Monitoring Committee (DMC)
- Funding for the trial ceases

The Research Ethics Committee will be notified in writing within 90 days when the trial has been concluded or within 15 days if terminated early.

### 3. METHODS AND ASSESSMENTS

#### 3.1 Schedule of delivery of intervention and data collection

**Table 1** Trial assessments

| Visit                                      | 1                | 2        | 3                               | 4                                | 5                                  | 6                                  | 7                               | 8                               | 9                               |
|--------------------------------------------|------------------|----------|---------------------------------|----------------------------------|------------------------------------|------------------------------------|---------------------------------|---------------------------------|---------------------------------|
| Visit Window
(No. Weeks $\pm$ No. Days) | Pre -
Consent | Baseline | 6wk
( $\pm$ 2wk)
After V2 | 10wk
( $\pm$ 2wk)
After V2 | 16 wk
( $\pm$ 4 wk)
After V2 | 24 wk
( $\pm$ 4 wk)
After V2 | 12 m
( $\pm$ 1m)
After V2 | 18 m
( $\pm$ 1m)
After V2 | 24 m
( $\pm$ 1m)
After V2 |
| Eligibility Check                          | ✓                |          |                                 |                                  |                                    |                                    |                                 |                                 |                                 |
| Written and verbal information provided    | ✓                |          |                                 |                                  |                                    |                                    |                                 |                                 |                                 |
| Written informed consent                   |                  | ✓        |                                 |                                  |                                    |                                    |                                 |                                 |                                 |
| Baseline CRFs (Pre and Post injury)        |                  | ✓        |                                 |                                  |                                    |                                    |                                 |                                 |                                 |
| Randomisation                              |                  | ✓        |                                 |                                  |                                    |                                    |                                 |                                 |                                 |
| Intervention delivery                      |                  | ✓        |                                 |                                  |                                    |                                    |                                 |                                 |                                 |
| OMAS                                       |                  | ✓        | ✓                               | ✓                                | ✓                                  | ✓                                  |                                 |                                 | ✓                               |
| MOXFQ                                      |                  | ✓        |                                 |                                  | ✓                                  |                                    |                                 |                                 |                                 |
| DRI                                        |                  | ✓        | ✓                               | ✓                                | ✓                                  | ✓                                  |                                 |                                 | ✓                               |
| EQ5D5L                                     |                  | ✓        | ✓                               | ✓                                | ✓                                  | ✓                                  | ✓                               | ✓                               | ✓                               |
| Resource use questionnaires                |                  |          | ✓                               | ✓                                | ✓                                  | ✓                                  | ✓                               | ✓                               | ✓                               |
| Complications                              |                  |          | ✓                               | ✓                                | ✓                                  | ✓                                  |                                 |                                 | ✓                               |

### 4. ADVERSE EVENT MANAGEMENT

#### 4.1 Definitions

##### 4.1.1 Adverse Events (AE)

An Adverse Event (AE) is defined as any untoward medical occurrence in a participant which does not necessarily have a causal relationship with this treatment/intervention. AEs related to the management of an ankle fracture will be recorded on the appropriate CRF for routine return to the AIR central office and reported to the relevant oversight committees.

##### 4.1.2 Serious Adverse Events (SAEs)

An AE is considered a SAE if it is an untoward medical occurrence that fulfils one or more of the following criteria:

- Results in death
- Is immediately life-threatening
- Requires hospitalisation or prolongation of existing hospitalisation
- Results in persistent or significant disability or incapacity
- Is a congenital abnormality or birth defect

- Is an important medical condition.

SAEs that are determined by the local PI to have no causal relationship with the intervention will not be required for onward reporting to relevant oversight committees.

#### 4.1.3 Expected Serious Adverse Events (SAEs)

SAEs that may be expected as part of the interventions are: complications of anaesthesia or surgery (e.g. wound complications, infections, damage to a nerve or blood vessel and thromboembolic events) and secondary operations for or to prevent infection, malunion, non-union or for symptoms related to the metalwork. These will be recorded on the participant's CRF for routine return to the AIR central office and reported to the relevant oversight committees. All participants experiencing SAEs will be followed-up as per protocol until the end of the 2 year follow up period.

### 4.2 Reporting AEs and SAEs

All AEs and SAEs will be entered onto the appropriate reporting form and reported to WCTU using a dedicated AIR and QA resource account within 24 hours of the investigator becoming aware of them. Once received, causality and expectedness will be confirmed by the Chief Investigator. SAEs that are deemed to be unexpected and possibly, probably or definitely related to the trial interventions will be notified to the Research Ethics Committee (REC) within 15 days. All such events will be reported to the TMG at their next meeting. All SAEs that occur between the date of consent and the end of two year follow up for the participant will be reported. For each SAE the following information will be collected:

- full details in medical terms and case description
- event duration (start and end dates, if applicable)
- action taken
- outcome
- seriousness criteria
- causality (i.e. relatedness to intervention), in the opinion of the investigator
- whether the event would be considered expected or unexpected.

| Relationship to trial intervention | Description                                                                                                                                                                                                                                                                                                                 |
|------------------------------------|-----------------------------------------------------------------------------------------------------------------------------------------------------------------------------------------------------------------------------------------------------------------------------------------------------------------------------|
| Unrelated                          | There is no evidence of any causal relationship                                                                                                                                                                                                                                                                             |
| Unlikely to be related             | There is little evidence to suggest there is a causal relationship (e.g. the event did not occur within a reasonable time after administration of the trial intervention or device). There is another reasonable explanation for the event (e.g. the patient's clinical condition, other concomitant treatment).            |
| Possible relationship              | There is some evidence to suggest a causal relationship (e.g. because the event occurs within a reasonable time after administration of the trial intervention or device). However, the influence of other factors may have contributed to the event (e.g. the patient's clinical condition, other concomitant treatments). |

|                       |                                                                                                                    |
|-----------------------|--------------------------------------------------------------------------------------------------------------------|
| Probable relationship | There is evidence to suggest a causal relationship and the influence of other factors is unlikely.                 |
| Definitely related    | There is clear evidence to suggest a causal relationship and other possible contributing factors can be ruled out. |

Once received by the AIR trial office all AEs and SAEs will be placed in one of two categories for onward reporting to oversight committees:

1. Local event (e.g. fracture non-union).
2. Systemic event (e.g. deep vein thrombosis).

### **4.3 Responsibilities**

#### Principal Investigator (PI):

Checking for SAEs and AEs when participants attend for treatment / follow-up.

1. Using clinical judgement in assigning seriousness, causality and expectedness
2. Ensuring that all SAEs are recorded and reported to the Sponsor within 24 hours of becoming aware of the event and provide further follow-up information as soon as available.
3. Ensuring that AEs are recorded.

#### Chief Investigator (CI) / delegate or independent clinical reviewer:

1. Clinical oversight of the safety of patients participating in the trial, including an ongoing review of the risk / benefit.
2. Using clinical judgement in confirming seriousness, causality and expectedness of SAEs.
3. Using clinical judgement in assigning expectedness.
4. Immediate review of all related and unexpected SAEs
5. Ongoing review of specific SAEs in accordance with the trial risk assessment and protocol as detailed in the Trial Monitoring Plan.
6. Production and submission of annual reports to the relevant REC.

#### Sponsor:

1. Central data collection and verification of SAEs, according to the trial protocol.
2. Reporting safety information to the CI, delegate or independent clinical reviewer for the ongoing assessment of the risk / benefit according to the Trial Monitoring Plan.
3. Reporting safety information to the independent oversight committees identified for the trial (Data Monitoring Committee (DMC) and / or Trial Steering Committee (TSC)) according to the Trial Monitoring Plan.
4. Expedited reporting of related and unexpected SAEs to the REC within required timelines.
5. Notifying Investigators of related and unexpected SAEs that occur within the trial.

#### Trial Steering Committee (TSC):

In accordance with the Trial Terms of Reference for the TSC, periodically reviewing safety data and liaising with the DMC regarding safety issues.

#### Data Monitoring Committee (DMC):

In accordance with the Trial Terms of Reference for the DMC, periodically reviewing unblinded overall safety data to determine patterns and trends of events, or to identify safety issues, which would not be apparent on an individual case basis.

#### **4.4 Notification of deaths**

Only deaths that are assessed to be caused by the intervention will be reported to the sponsor. This report will be immediate.

#### **4.5 Reporting urgent safety measures**

If any urgent safety measures are taken the CI/Sponsor shall immediately and in any event no later than 3 days from the date the measures are taken, give written notice to the relevant REC of the measures taken and the circumstances giving rise to those measures.

### **5. DATA MANAGEMENT**

Personal data collected during the trial will be handled and stored in accordance with the 1998 Data Protection Act.

The Case Report Forms will be designed by the TM in conjunction with the TMG. All electronic patient-identifiable information will be held on a secure, password-protected database accessible only to authorised personnel. Paper forms with patient-identifiable information will be held in secure, locked filing cabinets within a restricted area of Warwick Medical School. All subsequent CRFs will identify participants by a trial number only. Direct access to source data/documents will be required for trial related monitoring. All paper and electronic data will be retained for at least ten years after completion of the trial.

If any confidential information is disclosed by a participant indicating an issue which may jeopardise the safety of the participant or another person, such information will be brought to the attention of the CI and their treating clinical team as appropriate so an appropriate course of action can be determined.

#### **5.1 Data collection and management**

The CRFs will be developed to collect all required trial data. Suitably trained members of the research team will then complete and return CRFs to the AIR trial office. The AIR team will check and enter the data onto the trial database following instructions set out in the data management plan and in accordance with WCTU SOPs.

Suitably trained members of the research team will be required to complete CRFs at baseline and any occurring SAEs on an ongoing basis. All other outcomes/CRFs will be collected directly from the trial participants by postal mechanisms at the follow up time points. Participants will receive a £5 voucher incentive within the 16 week follow up questionnaire to aid retention and return. Procedures for chasing missing data/unreturned questionnaires are outlined in the data management plan.

#### **5.2 Database**

The database will be developed by the Programming Team at WCTU and all specifications (i.e. database variables, validation checks, screens) will be agreed between the programmers and appropriate trial staff.

### **5.3 Data storage**

All essential documentation and trial records will be stored by WCTU in conformance with the applicable regulatory requirements and Warwick SOPs. Access to stored information will be restricted to authorised personnel only.

### **5.4 Data access and quality assurance**

Personal data collected during the trial will be handled and stored in accordance with the 1998 Data Protection Act. All electronic patient-identifiable information will be held on a secure, password-protected database accessible only to authorised personnel. Paper forms with patient-identifiable information will be held in secure, locked filing cabinets within a restricted area of Warwick Medical School. All subsequent CRFs following baseline, will identify participants by a trial number only. Direct access to source data/documents will be required for trial related monitoring. All paper and electronic data will be retained for at least ten years after completion of the trial.

All names and addresses of trial participants will not be disclosed to anyone other than relevant members of the trial team. The investigator must arrange for retention of trial records on site in accordance with GCP. Direct access to source data/documents will be required for trial-related monitoring or audit by WCTU, internal audit, regulatory authorities and ethics committees.

Access to the final data set will be limited to authorised personnel at Warwick CTU and co-investigators, subject to local data sharing agreements.

### **5.5 Data Shared with Third Parties**

Any application received by third parties will be discussed and approval sought by the TMG. Relevant data sharing agreements would be put in place.

### **5.6 Archiving**

Trial documentation and data will be archived for at least ten years after completion of the trial, in keeping with WCTU SOPs.

## **6. STATISTICAL ANALYSIS**

### **6.1 Power and sample size**

The primary outcome for this study is the OMAS 16 weeks post injury. The OMAS is measured on a scale between 0 and 100, where higher scores denote better function. The minimum clinically important difference (MCID), or smallest between group difference that is likely to be clinically meaningful beyond measurement error for foot and ankle conditions is a change of 10 points. This is consistent with the AIM study [14], which set the OMAS equivalence margin between groups to be 6 points. It is also consistent with other similar outcome measures such as the Foot and Ankle Outcome Score [15], and visual analogue pain scores in acute injury; that report MCIDs of approximately 10 points on a 100 point scale.

The standard deviation (SD) of the OMAS at six months after injury from previous feasibility work was approximately 28 points. To account for any variation arising from recruiting from multiple study centres and to allow that the primary outcome has been moved from this time point, we have selected a conservative estimation of the trial SD of 30 points. This corresponds to a moderate standardised effect size of 0.33. Hence, the total trial sample size required to detect a difference of

10 points given a SD of 30 points with two-sided significance set at 5% and 90% power is a minimum of 382 participants.

Allowing a margin of 20% loss during follow-up (whilst striving to keep this below 10%), this gives a figure of 478 participants in total. Therefore, a minimum of 239 participants randomised to each group will provide 90% power to detect a difference of 10 points in OMAS at sixteen weeks at the 5% level. If possible, recruiting a larger sample would enable the between group differences of the two groups to be estimated with higher precision. The minimum 382 participants would create a 95% CI of width 8.5 points. If, for example, 625 participants were recruited, this would yield data on around 500 participants at 20% loss to follow up and would enable a 95% confidence interval (CI) of width 7.4 points to be constructed.

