## **2. TRIAL DESIGN**

### **2.1 Trial summary and flow diagram**

This is a UK multi-centre, randomised controlled trial. All adults with a fractured ankle under the care of a clinician at any of the named recruiting sites are potentially eligible. New patients with an ankle fracture are reviewed each day by the trauma team either:

1. As an inpatient admission on the trauma ward.
2. As an outpatient in fracture clinic.

Following identification of a potential participant with a new ankle fracture by the trauma team a suitably trained member of the research team at each site will be contacted to undertake eligibility checks in conjunction with the trauma team.

All adults with an ankle fracture for which the treating clinician would consider cast a reasonable management option will be assessed for study entry. All potential participants meeting the entry criteria will be checked for eligibility and details entered on the monthly screening log. All eligible potential participants who are willing to be approached by a suitably trained member of the research team will be provided with verbal and written information about the study. At which point they will follow one of two pathways:

1. Deemed appropriate for surgery and placed/waiting to be placed on a suitable trauma list to undergo surgery. Following surgery, they will be managed as per normal clinical practice at each participating site to allow the wound to heal and discharged home. They will then return to an outpatient clinic to check the wound is healing satisfactory by the trauma team (usually second week post op). At this time if the wound assessment is satisfactory a suitably trained member of the research team will re-approach the participant to confirm eligibility with the trauma team.
2. Deemed not appropriate for surgery. In these cases the suitably trained member of the research team will approach the participant to confirm eligibility with the trauma team.

If a potential participant is deemed eligible and is willing to take part in the study, a suitably trained member of the research team will then be responsible for completing consent procedures, baseline demographic data and pre and post injury functional outcomes using OMAS, DRI and EQ-5D-5L before randomisation. The participant will then be randomised using a web based randomisation service to either the FARO intervention or the cast control, on a 1:1 basis, stratified by centre, age and operative/non-operative management.

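### The planned 95% CI widths of 8.5 and 7.4 points are those of one arm's mean; for the between-group difference they are about 12.0 and 10.5

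*Protocol*

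**What the plan says.** Protocol section 6.1 plans on an SD of 30 for the OMAS: "we have selected a conservative estimation of the trial SD of 30 points". The feasibility SD was a little lower: "from previous feasibility work was approximately 28 points". The target difference is 10 points, which the section also gives as the MCID, and the standardised effect is 0.33. The sample size statement reads: "10 points given a SD of 30 points with two-sided significance set at 5% and 90% power is a minimum of 382 participants". With 20% loss added, this becomes 478 randomised. Section 2.1 sets allocation "on a 1:1 basis, stratified by centre, age and operative/non-operative management".

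Section 6.1 then turns to precision. It says that "recruiting a larger sample would enable the between group differences of the two groups to be estimated with higher precision" and illustrates this with two figures. For the minimum: "The minimum 382 participants would create a 95% CI of width 8.5 points". For a scenario of 625 recruited and about 500 analysed, the data "would enable a 95% confidence interval (CI) of width 7.4 points to be constructed".

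**The concern.** The sentence that introduces the two widths is about the difference between the groups, and no other quantity is named. A width of 8.5 at 382 participants does not fit the power statement in the same section. Ninety per cent power for 10 points at two-sided 5% fixes the standard error of the difference at about 3.1, hence a 95% interval about 12 points wide.

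Two things are at stake. Precision is the only reason the section gives for recruiting more than the minimum, and both figures offered in support are too favourable. A reader such as the DMC, the TSC or the funder would also expect a more decisive trial than the one planned, particularly if the result falls between zero and the MCID.

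**Working it through.** **Inputs** (Protocol sections 6.1 and 2.1): SD 30; difference 10; two-sided 5%; 90% power; 1:1 allocation; 382 analysed (191 per arm); about 500 analysed (250 per arm, from 625 × 0.8).

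**1. The plan's sample size reproduces.** The standardised effect is 10/30 = 0.33. The t-based requirement is 190.1 per arm, so 191 per arm and 382 in total. 382/0.8 = 477.5, so 478. Power at 191 per arm is 90.3%. The section therefore uses the full SD of 30, with no allowance for covariates.

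**2. Width for the between-group difference.** Full width = 2 × 1.96 × SD × √(2/n per arm).

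- 191 per arm: SE = 30 × √(2/191) = 3.07; width 12.03 (12.07 with the t quantile); half-width 6.0.
- 250 per arm: SE = 30 × √(2/250) = 2.68; width 10.52 (10.54 with t); half-width 5.3.

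**3. Where the printed figures come from.** Full width for one arm's mean = 2 × 1.96 × SD/√(n per arm).

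- 191: 2 × 1.96 × 30/√191 = 8.51, printed as 8.5.
- 250: 2 × 1.96 × 30/√250 = 7.44, printed as 7.4.

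Both match to the printed decimal. The other readings tried do not:

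| Reading | 382 analysed | 500 analysed |
|---|---|---|
| Printed | 8.5 | 7.4 |
| One arm's mean, full width | 8.51 | 7.44 |
| Difference, full width | 12.03 | 10.52 |
| Difference, half-width | 6.02 | 5.26 |
| Difference, SD 28, full width | 11.23 | 9.82 |
| Difference, 90% CI, full width | 10.10 | 8.83 |
| One mean over all participants, full width | 6.02 | 5.26 |

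The ratios of correct to printed width are 12.03/8.5 = 1.415 and 10.52/7.4 = 1.422, against √2 = 1.414.

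**4. Consistency with the stated power.** 90% power needs SE = 10/(1.96 + 1.28) = 3.09, a width of 2 × 1.96 × 3.09 = 12.1. A width of 8.5 implies SE = 8.5/3.92 = 2.17, and power of Φ(10/2.17 − 1.96), about 99.6%. On one set of assumptions, 382 participants cannot give both 90% power and a width of 8.5.

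**5. Could covariate adjustment explain it?** A width of 8.5 at 382 needs a residual SD of 8.5/(3.92 × √(4/382)) = 21.2. That means an R² of 1 − (21.2/30)² = 0.50, or a correlation with baseline of about 0.71 (0.65 if the SD is 28).

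**6. What a result at 382 analysed could rule out.**

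- Printed width (±4.25): intervals exclude zero for estimates above 4.25 and exclude 10 for estimates below 10 − 4.25 = 5.75. No interval contains both.
- Correct width (±6.02): intervals exclude zero above 6.02 and exclude 10 below 10 − 6.02 = 3.98. Estimates from about 4 to 6 leave both open. An estimate of 5 gives about −1.0 to 11.0, where the printed width would give 0.75 to 9.25.

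**7. Scale of the gap.** Widths of 8.5 and 7.4 for the difference would need 4 × (117.6/8.5)² ≈ 766 and 4 × (117.6/7.4)² ≈ 1,010 analysed, where 117.6 = 2 × 1.96 × 30.

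**The case against.** The arithmetic is hard to contest; the case on the other side is about consequence.

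- **The widths are illustrative.** Section 6.1 offers 625 only as an example to follow if possible, sets no target width, and does not use the figures elsewhere. The planned minimum stays at 478, so the 766 and 1,010 above measure the size of the error, not a shortfall in the trial. This stands.
- **The relative gain from a larger sample is unchanged.** Both figures carry the same factor: 7.4/8.5 = 0.87 and 10.52/12.03 = 0.87. Going to 625 still narrows the interval by about 13%, and the absolute gain is slightly larger (1.5 points rather than 1.1). This stands too: the direction of the argument survives and only the stated values are wrong.
- **Comparing a full width with the MCID can mislead.** With an observed difference of zero, the correct interval of about ±6 still excludes 10. That is true, but the full width decides whether one interval can hold both zero and 10. At 8.5 it cannot; at 12.0 it can. The affected band is narrow, about 4 to 6 points, but it is where a non-significant result would be hardest to interpret.
- **The widths may refer to the adjusted model.** Section 6.2.3.2 makes a baseline-adjusted mixed model primary, and an R² near 0.50 would give similar widths. This cannot be wholly excluded. However, the section states no correlation or residual SD, its 382 uses the unadjusted SD, and the match to the single-arm formula is close in both cases. Adjusted widths set beside an unadjusted sample size without saying so would also need correction.

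The final interval will come from the trial data, so the planning figures do not bias the reported result.

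**Conclusion.** The concern holds. As precision of the between-group difference, the two widths in section 6.1 are understated by about 29 to 30%: 12.0 rather than 8.5 points at 382 analysed, and 10.5 rather than 7.4 at 500. This rests on SD 30, equal arms and no covariate gain, the same assumptions that reproduce the 382. With the feasibility SD of 28 the widths would be 11.2 and 9.8, still well above those printed. That the single-arm formula was used is an inference from the numerical match, since the section shows no formula; that the figures are wrong for the difference at SD 30 does not depend on it. The error is confined to the precision statement and leaves the sample size, power and analysis intact.

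**What to change.** In section 6.1, replace the two widths. State that 382 analysed gives an expected 95% CI for the between-group difference of about 12.0 points full width (±6.0), and 500 analysed about 10.5 points (±5.3), both at SD 30 and before covariate adjustment. Say explicitly whether full or half width is meant. Restate the case for exceeding 478 with these numbers; the 13% relative narrowing can be kept. If adjusted precision was intended, give the assumed R² or baseline correlation and its source, and label the widths as adjusted.

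The cost is two numbers and a short qualifying phrase, with a less favourable statement of precision. The 382, the 478 and the analysis need no change.
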